# The physical activity at work (PAW) study protocol: a cluster randomised trial of a multicomponent short-break intervention to reduce sitting time and increase physical activity among office workers in Thailand

**DOI:** 10.1186/s12889-020-09427-5

**Published:** 2020-09-01

**Keywords:** Sedentary behaviour, Physical activity, Productivity, Behaviour change techniques, Quality of life, Non-communicable diseases, Multicomponent intervention, Cost-effectiveness

## Abstract

**Background:**

High levels of sedentary behaviour (SB) are associated with non-communicable diseases. In 2016, the estimated total healthcare expenditure from physical activity (PA) in Thailand added up to $190 million in international dollars. The challenge to reduce SB and increase PA among office workers is more urgent now than ever as Thailand is transforming itself from a predominantly rural country to an increasingly urban one. This study will investigate the effectiveness of a multicomponent short break intervention on the reduction of SB during office hours.

**Methods/design:**

This two-armed Physical Activity at Work (PAW) cluster randomised controlled trial will recruit 360 office workers from 18 offices in the Thailand’s Ministry of Public Health (MOPH). Offices will be randomised to either the intervention group or the control group. The multicomponent intervention is informed by the Social Ecological Model and Behaviour Change Techniques (BCTs) and contains four components: (i) organisational, including heads of the participating divisions leading exercises, sending encouragement text messages and acknowledging efforts; (ii) social, including team movement breaks and team-based incentives; (iii) environmental, including posters to encourage exercise; and (iv) individual components including real-time PA feedback via an individual device. The main intervention component will be a short break intervention. The primary outcome of this study is the sedentary time of office workers. Secondary outcomes include time spent on PA, cardiometabolic outcomes, work productivity, musculoskeletal pain, and quality of life. The study also includes process and economic evaluations from the individual and societal perspective.

**Discussion:**

The study will be the first experimental study in Thailand to investigate the effect of a short-break intervention at the workplace on SBs of office workers and health outcomes. The study will also include a cost-effectiveness analysis to inform investments on short break interventions under the Universal Healthcare Coverage in Thailand, which includes health promotion and disease prevention component.

**Trial registration:**

The PAW study has been registered at the Thai Clinical Trials Registry (TCTR) under the study ID TCTR20200604007. Registered 02 June 2020,

## Background

The negative effects of sedentary behaviour (SB) and a lack of physical activity (PA) on health have been well documented [1–8]. SB is defined as any waking time activity during which one is seated, reclined or lying, having an energy expenditure ≤1.5 metabolic equivalents (METs), while PA is defined as any activity with an energy expenditure > 1.5 METs [9–11]. High levels of SB are associated with a 112% increase in the risk of diabetes, 147% increase in the risk of cardiovascular disease, 90% increase in the risk of cardiovascular mortality and 49% increase in the risk of all-cause mortality [4]. In addition, SB has detrimental associations with fasting glucose, fasting insulin, triglycerides, high-density lipoprotein cholesterol and waist circumference [1].

The negative effects of the behaviour have also been studied in Thailand. According to recent estimates, 6.3% of all-cause mortality in Thailand is due to physical inactivity [12]. The estimated total healthcare costs from physical inactivity in Thailand accounted for $190 million in international dollars (INT$ was calculated using purchasing power parity conversion factors from 2013) [13]. The proportion of individuals not meeting 150 min of moderate-to-vigorous PA in Thailand have increased from 18.5% in 2008 to 19.2% in 2014 [14]. According to the Thai Health Promotion Foundation, Thais spend on average 2 h a day engaging in PA and about 13 h in SB [14].

A long-studied effect of urbanisation is the transition from jobs with more manual work (such as agriculture) to non-manual service jobs that are typically desk-bound [15]. Typical office workers spend most of their SB hours at the office. This is particularly true for computer-based occupations, where employees spend a substantial amount of time in uninterrupted sitting [16–18]. A study found that office-based workers spent up to 75.8% of their working time sitting [19]. Further, breaks between these sitting times were uncommon, with 25% of the total sitting time in bouts of 55 or more minutes [17]. This directly translates to a lower energy expenditure, where such workers expended around ~ 700 kcals/day, compared to individuals whose jobs require some manual labour (~ 2300 kcals/day) [20]. As work-time contributes significantly to the total sedentary time, working hours are an important avenue to address movement behaviours.

It has been suggested that one way to attenuate the negative effects of SB is to increase PA. Studies have illustrated that after adjusting for PA, the negative associations with SB were less pronounced [2, 5]. Physical inactivity represents the non-achievement of PA guidelines, and based on the World Health Organisation global recommendations on PA for health state, adults should do at least 150 min of moderate-intensity aerobic PA throughout the week [21]. Having short PA breaks during working hours can help office workers meet these recommendations.

Short break interventions in the workplace have shown reductions in sedentary time [22]. However, mixed results have been found for their impact on intermediate health outcomes such as calories spent, cholesterol (HDL-C and LDL-C), triglycerides, fasting blood glucose, blood pressure and stress level [22–30]. Importantly, results of a recent randomised trial showed that taking two long breaks (15 min) per workday is less effective than taking shorter breaks (1-2 min) every 30 min [22, 24]. In this study, the long-break group had no change in health outcomes while the short-break group had small-to-moderate declines in total cholesterol (d = − 0.33; *p* = 0.10), triglycerides (d = − 0.38; *p* = 0.06), and fasting blood glucose (d = − 0.29, *p* = 0.01). Even though short breaks every half an hour seems to be more clinically effective, it is less likely to be feasible and scalable in real world practice. Moreover, the above studies were conducted only in high-income countries. No study has investigated the effects of a short-break intervention on the reduction on SB and its impacts on health and productivity outcomes at the workplace in low- and middle-income countries where the majority of metabolic diseases occurs. This study aims to fill this gap.

The study is designed as a two parallel-group cluster randomised superiority trial. The primary outcome assesses sedentary time at the 6th month. The aims of the study are to evaluate (i) the impact of a multicomponent short-break office intervention on minutes spent sedentary during office hours. In addition, the study will also evaluate the effect of the intervention on secondary outcomes such as PA, cardiometabolic risk factors and productivity (ii) the sustainability of the behavioural change; and (iii) the cost-effectiveness of the short-break office intervention. The cost-effectiveness analysis will allow the results to be compared with other trials’ economic evaluations. The results of this study will assist the Thai government in developing health promotion and disease prevention benefit package under the Universal Healthcare Coverage (UHC) scheme. Filling this knowledge gap might also help inform investments on short break interventions in the private sectors.

## Method

### Study design

#### Setting

The study will be located at the Department of Medical Services (DMS), Thailand’s Ministry of Public Health (MOPH) in Nonthaburi Province. Employees are working in central offices with fixed desks. Work tasks comprise mostly computer-based work, but also involve meetings and travelling to meet with officers from other ministries. The offices are all located in the same building on levels 2 to 6.

#### Study design and randomisation

This study is a stratified cluster randomised controlled trial with two arms. We will include at least 18 offices (9 offices per arm) from the DMS, MOPH, forming five strata. These strata are chosen by office sizes (< 15, 15-20, 21-25, 26-34 and ≥ 35 participants). Block randomisation with block sizes of two, four and six will be used to generate the randomised sequence for each stratum. Cluster randomisation by offices minimises the problem of cross-contamination between the intervention arms due to environmental changes in the offices.

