#### Blinding

At baseline data collection, participants and data collectors will be blinded to group allocation. Randomisation and allocation of intervention will be performed after the completion of baseline data collection, and participants will be notified via email by researchers not involved in data collection. The allocation sequence will be generated using a computer program which will be created for each stratum. Due to the nature of the intervention, participants are required to know whether they are in the intervention or control group and does not allow for blinding. At follow-up measurements, participants and data collectors will know the treatment allocation. The involvement of research teams from different institutions and countries will allow one team to conduct the randomisation, another to conduct the analysis, and the team from Thailand will implement the trial and perform the data collection. This will ensure that the researchers conducting the analysis will be blinded to the assignment. The analyst will only know the study identifier but not the participant’s name, identifiers, and treatment allocation. Participants’ data (e.g. case record forms, laboratory test, information sheets, and consents) will be stored in a locked cabinet in a researchers’ office. All data will be destroyed by researchers within 5 years after publications. The study protocol has been registered at Thai Clinical Trials Registry (TCTR20200604007) [31]. The study also follows the recommendations of the SPIRIT guidelines. A SPIRIT checklist with references to the relevant page numbers of this protocol is provided (see Additional file 3).

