#### Sample size

Eligible office workers from the DMS will be invited to participate in the trial. To detect a difference in the primary outcome of 23.3 min in sedentary time per day as reported in a prior randomised trial [22], the sample size was calculated with a standard deviation (SD) of 45.5, based on a two-tailed significance level of 5% and power of 80%. The calculation assumes a conservative intra-cluster correlation coefficient of 0.05 and a coefficient of variation of 0.52 to account for varying cluster sizes in the study. There are 18 clusters (offices), each cluster varying between 7 to 40 office workers. The mean cluster size was 22.1 with a standard deviation of 11.6. Assuming an average cluster size of 22 participants, we will yield a design effect of 2.36. Therefore, the total sample size required to detect a difference of 23.3 min in SB is 288 participants. To conform to best practice, this sample size will be inflated by 20% to account for dropouts and potential loss of participants due to non-compliance to primary outcome or chances of faulty devices. Hence, a sample size of 360 participants is needed.

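### Blocks of two, four and six within five strata of about 18 offices do not guarantee the stated 9 offices per arm; a single constrained draw after baseline would, at no cost

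*Protocol article*

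**What the plan says.** All but the last two points below come from the Study design and randomisation and Blinding sections of the protocol article.

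- Offices and split: "We will include at least 18 offices (9 offices per arm) from the DMS, MOPH, forming five strata".
- Strata: "These strata are chosen by office sizes (< 15, 15-20, 21-25, 26-34 and ≥ 35 participants"). The number of offices in each band is not given.
- Method: "Block randomisation with block sizes of two, four and six will be used to generate the randomised sequence for each stratum". The section does not say whether the three lengths are mixed at random or fitted to each stratum, or what happens to an incomplete block.
- Sequence generation, under Blinding: "The allocation sequence will be generated using a computer program which will be created for each stratum".
- Timing, also under Blinding: "Randomisation and allocation of intervention will be performed after the completion of baseline data collection".
- The Sample size section gives 18 offices of 7 to 40 workers, mean 22.1 and SD 11.6.
- The Data analyses section lists the office-size stratum among the covariates, but only for use where needed.

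**The concern.** Permuted blocks balance the arms only when a block is completed. Five strata sharing 18 offices hold 18/5 = 3.6 offices each on average, so a block of four or six often runs past the end of its stratum. The leftover imbalances then add up across strata, and nothing in the described scheme makes them cancel.

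Mixing block lengths protects a sequential enrolment from prediction. Here the offices can all be known before the list is made, so that protection buys little and costs balance. Two things are at stake. One is the 9 per arm given in the same section. The other is balance on office size, the only factor chosen for stratification, in a trial whose offices vary almost sixfold in size (40/7 = 5.7).

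**Working it through.** **1. The plan's own sample size.** The inputs are "To detect a difference in the primary outcome of 23.3 min in sedentary time per day", SD 45.5, two-sided 5%, 80% power, and "intra-cluster correlation coefficient of 0.05 and a coefficient of variation of 0.52". The t-based two-sample calculation gives 60.8, so 61 per arm and 122 in total. The design effect is 1 + ((CV² + 1)m − 1) × ICC. With m = 22.1 and CV = 11.6/22.1 = 0.525 it is 1 + (1.2755 × 22.1 − 1) × 0.05 = 2.36. Then 122 × 2.36 = 287.9, so 288, and 288/0.8 = 360. The stated figures reproduce.

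**2. Assumptions for the allocation check.** There are exactly 18 offices. Each block length of 2, 4 or 6 is equally likely. The last block in a stratum is cut at the stratum's size. Stratum counts are unknown, so all 57 ways of dividing 18 offices into five non-empty strata were enumerated exactly.

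**3. Chance that one stratum falls wholly in one arm.**

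- One office: always, under any scheme.
- Two offices: block of 2 gives 0, block of 4 gives 2/6 = 1/3, block of 6 gives 2 × 3/15 = 2/5. The mean is (0 + 1/3 + 2/5)/3 = 11/45 = 24.4%.
- Three offices: only a block of 6 allows it, 2 × 1/20 = 1/10. The mean is 1/30 = 3.3%.
- Four or more offices: impossible, since no block places more than three offices in one arm and completed blocks are balanced.

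Five strata of four or more would need 20 offices, so with 18 at least one stratum has three or fewer. The chance of at least one such stratum in one arm is 1 − (29/30)² = 6.6% for 3/3/4/4/4, the lowest of the 57 splits. For 2/2/4/4/6 it is 1 − (34/45)² = 43%.

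**4. Chance of 9:9 overall.** Strata of 2, 4 and 6 offices come out balanced with probability 0.756, 0.785 and 0.847. For 2/2/4/4/6, all five balance with probability 0.756² × 0.785² × 0.847 = 0.30. Imbalances that happen to offset one another raise the chance of 9:9 to 0.41. Results of the enumeration:

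| Result | Range over the 57 splits |
|---|---|
| Exactly 9:9 | 32-42% |
| 11:7 or worse | 12-21% |
| 12:6 or worse | about 1-3% |

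**5. The alternative reading.** If each stratum instead had one block equal to its size, 9:9 would be exact and no stratum would be lost to one arm. With the three stated lengths this needs every stratum to hold exactly 2, 4 or 6 offices. Three of the 57 splits qualify: 2/2/4/4/6, 2/4/4/4/4 and 2/2/2/6/6. Office sizes consistent with the stated range, mean and SD exist for some of these.

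**6. Effect on power.** The effective sample is 288/2.36 = 122.0. With a fraction p of it in one arm, SE = 45.5 × √(1/(122.0p) + 1/(122.0(1 − p))), and power = Φ(23.3/SE − 1.96). As a check, an office-level t-test was run with 288/18 = 16 per office and 18 − 2 − 4 = 12 degrees of freedom. Its design effect is 1 + (1.2704 × 16 − 1) × 0.05 = 1.966.

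| Split | SE (normal) | Power (normal) | Power (t, 12 df) |
|---|---|---|---|
| 9:9 | 8.24 | 80.7% | 81.2% |
| 10:8 | 8.29 | 80.3% | 80.7% |
| 11:7 | 8.45 | 78.8% | 79.2% |
| 12:6 | 8.74 | 76.0% | 76.5% |

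**The case against.** The article never says that block lengths are drawn at random. With every office known after baseline, the wording also permits a block fitted to each stratum, and for some stratum counts that gives 9:9 exactly. The office count is open (at least 18, with further departments possible if participation is low), so 9 per arm may be only a 1:1 target. Stratified permuted blocks are a valid method, and a journal article may leave list-generation detail to the full protocol.

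Much of this stands. A reader might infer that the scheme cannot produce 9:9 at all. The text does not support that: even mixed blocks reach it in about a third or more of draws, and fitted blocks could reach it always. The fitted reading is nevertheless narrow. It works in 3 of the 57 splits, the section does not mention it, and naming three lengths for each stratum's sequence more naturally means mixing them.

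A reader might also infer that a one-arm stratum confounds office size with treatment and biases the result. Chance imbalance under valid randomisation does not bias the estimate. Such a stratum adds little or no within-stratum comparison, which is a loss of precision. The analysis section already allows adjustment for the stratum, although it does not commit to it.

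**Conclusion.** The concern holds as a lack of guarantee. As described, the scheme does not secure 9 offices per arm or balance on office size. Under the more natural reading, it misses 9:9 in 58-68% of draws, and this does not depend on the unknown stratum counts. The figures do depend on equal chances for the three lengths, a truncated last block and exactly 18 offices. The one-arm risk also depends heavily on how many strata hold three offices or fewer.

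The consequence is modest. In about 79-88% of draws the split is 9:9 or 10:8, where power moves by half a point. At 11:7 the loss is about 2 points, and at the rare 12:6 about 5. The documents do not support calling the trial under-powered on this account. The point is worth acting on because the remedy is free, the number of clusters is small, and the allocation is made once and cannot be undone.

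**What to change.** Replace the varying blocks with one computer draw made after baseline. List every allocation of the participating offices that has equal arm totals (differing by at most one if the number of offices is odd) and a difference of at most one office within each stratum. Pick one at random. Equivalently, use a block equal to each stratum's size and balance the odd offices across strata. Merge any one-office stratum with a neighbouring size band. Reword the Study design and randomisation section accordingly and give the number of offices per stratum.

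Ample randomness remains. For 2/2/4/4/6 there are 2 × 2 × 6 × 6 × 20 = 2,880 admissible allocations. For 3/3/4/4/4 there are 6³ × 2 × 3 × 3 = 3,888. Swapping the arms maps the list onto itself, so every office keeps a one-half chance of either arm.

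The cost is a change to the randomising team's program and a revised paragraph. No extra participants, offices or staff are needed, and the sample size stays as it is.

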#### Blinding

At baseline data collection, participants and data collectors will be blinded to group allocation. Randomisation and allocation of intervention will be performed after the completion of baseline data collection, and participants will be notified via email by researchers not involved in data collection. The allocation sequence will be generated using a computer program which will be created for each stratum. Due to the nature of the intervention, participants are required to know whether they are in the intervention or control group and does not allow for blinding. At follow-up measurements, participants and data collectors will know the treatment allocation. The involvement of research teams from different institutions and countries will allow one team to conduct the randomisation, another to conduct the analysis, and the team from Thailand will implement the trial and perform the data collection. This will ensure that the researchers conducting the analysis will be blinded to the assignment. The analyst will only know the study identifier but not the participant’s name, identifiers, and treatment allocation. Participants’ data (e.g. case record forms, laboratory test, information sheets, and consents) will be stored in a locked cabinet in a researchers’ office. All data will be destroyed by researchers within 5 years after publications. The study protocol has been registered at Thai Clinical Trials Registry (TCTR20200604007) [31]. The study also follows the recommendations of the SPIRIT guidelines. A SPIRIT checklist with references to the relevant page numbers of this protocol is provided (see Additional file 3).

### Participant recruitment

#### Inclusion and exclusion criteria

Office workers with the following criteria are eligible to participate in this trial: 1) have an end date for employment after the study completion date, 2) are legally able to consent, i.e. age 18 years and above, 3) do not have a disability on the upper or lower body that limits their mobility, 4) have a permanent office workstation within one of the clusters included in the trial, 5) works either from their permanent offices or at home at least 3 days a week 6) owns and uses a smartphone compatible with the Fitbit application and 7) are willing to be randomised into one of the two study interventions. Office workers will be excluded from the study if one is away on an extended leave or a personal retreat for more than 2 weeks or is pregnant.

#### Recruitment

While randomisation will be conducted at a cluster level, consent to participate will be sought on a cluster level by leaders, thereafter on the individual level. Office workers will be invited to participate in this study by email. Interested office workers will be screened for eligibility via an online survey. Candidates who meet the inclusion and exclusion criteria will be invited for baseline measurements. Prior to the measurements, study requirements will be explained again and written informed consent will be obtained. Participation will be voluntary, and participants can withdraw at any time without giving any reason. Participants will not face a penalty or consequences of any kind from withdrawing. If participants agree to participate in follow-up assessments after their withdrawal, researchers will conduct these assessments. Departments of MOPH that are not involved in short-break interventions will be considered if there is insufficient participation from DMS. During the recruitment phase, the research team will be in close contact with team leaders of the participating offices and will attend team meetings to facilitate recruitment when needed. To aid with the enrolment, information sessions about the study will be held at DMS.

